### Sample size

6.4

The calculation of the sample size is derived from the formula comparing two sample rates：$$N=\frac{{\left(Z_{1-\alpha \;}+Z_{1-\beta }\right)}^{2}\left(1+\frac{1}{k}\right)\cdot \sigma^{2}}{{\left(\mu_{T\;}-\mu_{C}-△\right)}^{2}})$$

Here, N represents the required sample size for each group, Pe and *Pc* denote the maximum and minimum effective rates of each group. Based on our retrospective clinical data and previous experimental reports, acupuncture demonstrated a reduction in FSH levels by 20 IU/L, while assuming that the control group reduced FSH levels by 14.5 IU/L. For the study, which is divided into two groups with parameters $\mu_{T\;}$ = 20, $\mu_{C}$ = 14.5, △=3, a test level α = 0.05 and a test efficiency 1-β = 0.9 were considered.

In light of an anticipated 20 % dropout rate, a total of 108 patients will be recruited, ensuring no less than 54 participants in each group. Given the absence of a standardized sample size calculation for transcriptome analysis, the approach aligns with prevalent studies on POI. From the pool of 108 participants, 10 patients in each group (comprising 5 with a decrease of ≥30 % in serum FSH levels after intervention, 5 with a decrease of <30 % in serum FSH levels after intervention, and 10 normal female volunteers in the healthy control group) will be selected for transcriptome analysis.

### Allocation and blinding

6.5

Participant allocation to either the study or control group will follow a meticulous 1:1 ratio, determined by adherence to predetermined inclusion and exclusion criteria. A prospective cohort study protocol has been devised for individuals diagnosed with POI, stratified by the extent of FSH decline. The exposure factor under investigation is acupuncture treatment, with categorization based on FSH decline exceeding 30 % or less than 30 %, comprising 5 cases each.

In this openly conducted clinical trial, recognition is accorded to the inherent awareness of both patients and involved acupuncturists regarding treatment assignments due to the study's nature. However, to counterbalance potential biases and uphold the scientific rigor of the investigation, specific measures will be instituted to ensure the maintenance of blinding for other pivotal personnel involved in the study.

### Data collection and management

6.6

Data collection will be conducted at two critical junctures: baseline and postintervention. Trained data collectors, employing case report forms (CRFs), will meticulously record participant information. Specifically, the anxiety and depression levels of participants will be assessed through the administration of the Self-Rating Anxiety Scale (SAS) and Self-Rating Depression Scale (SDS), respectively. Following the CRF-based data collection, the information will be meticulously entered into an electronic database to facilitate streamlined data management.

To bolster accuracy, a dual data entry system will be implemented, involving two data collectors to independently input the data, thereby minimizing errors. Subsequently, the clinical raw data will undergo scrutiny by the project supervisor, who will rectify any identified errors or inconsistencies before proceeding with data export. Once the data's accuracy is affirmed, the database will be securely locked, paving the way for subsequent statistical analyses. Participant identification will be maintained through assigned numbers, and the database will be password-protected to uphold confidentiality.

Oversight of the data will be conducted by the ethical review board of the Shenzhen Maternity and Child Healthcare Hospital. Comprehensive reporting on participant withdrawals and the reasons for withdrawal will be undertaken. In the event of dropouts, modern imputation methods for handling missing data will be employed, ensuring their inclusion in the subsequent analyses.

### Statistical methods

6.7

Data analysis will be executed utilizing SPSS version 25.0 (SPSS Inc., Chicago, IL, USA) by two qualified statisticians, ensuring the attainment of robust and reliable results.Descriptive statistics, comprising mean, median, 25th percentile, 75th percentile, standard deviation, maximum values, and minimum values, will be employed to present the results of the measurement data analysis. Group comparisons will be facilitated using either the independent sample *t*-test or the Mann-Whitney U rank sum test, contingent upon the normal distribution and homogeneous variance of the measurement data. Enumeration data will be characterized by frequency and constituent ratios, with group comparisons executed through Pearson's χ2 test or Fisher's exact test. Correlations between different indicators will be explored through Pearson and Spearman correlations. A significance threshold of P < 0.05, employing a two-sided test, will dictate statistical significance. Additionally, metagenomic analysis of the gut microbiome will be conducted by BGI Shenzhen Co., Ltd (China).

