### Primary outcome: change in FSH levels

5.1

The principal outcome measure in this study revolves around the alteration observed in FSH levels. This metric serves as a pivotal gauge to evaluate the effectiveness of acupuncture treatment when employed as an adjunctive therapy for POI. The data collection process is bifurcated into two distinct time points: the baseline assessment conducted prior to the study's initiation and a subsequent assessment following the culmination of three menstrual cycles of acupuncture treatments. This meticulous approach aims to provide comprehensive insights into the impact of acupuncture on FSH levels over the specified duration, thereby contributing to the overall assessment of its therapeutic efficacy for POI.

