### Bioinformatic and statistical analysis

6.2

Quantification of RNA sequencing data was executed utilizing the kallisto software [22]. Differential expression analysis was conducted with the DESeq2 package [23] to identify genes with distinct expression patterns. Additionally, the cluster Profiler package [24]

was employed to enhance the analysis of differentially expressed genes.

Continuous variables' normality was assessed using the Shapiro-Wilk test in this study. For normally distributed continuous variables, data were presented as mean ± SD (standard deviation), and intergroup comparisons utilized Student's t-test. Conversely, skewed continuous variables were expressed as median (interquartile range, IQR) and compared through the nonparametric Wilcoxon rank-sum test. Categorical variables were reported as frequencies (percentages, %) and subjected to comparison via the chi-square test.

To explore associations between gene abundance and various clinical indicators pertaining to ovarian reserve, ovarian endocrine function, and perimenopausal syndrome symptoms, Pearson's correlation analysis was employed. For genes exhibiting significant differences, receiver operating characteristic (ROC) curves were constructed to assess their diagnostic performance. The area under the curve (AUC) value served as a metric for discriminatory power. Statistical significance was set at a two-tailed *P* < 0.05. R software was utilized for all data analyses.

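### The primary FSH comparison picks a t-test or a Mann-Whitney test from the trial data and does not adjust for baseline FSH; one pre-named ANCOVA would cost nothing and fix the estimand

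*Protocol article*

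**What the plan says.** - **Outcome.** Section 5.1: "The principal outcome measure in this study revolves around the alteration observed in FSH levels", assessed before the study and again after three menstrual cycles.
- **Data available.** Section 6.6: "Data collection will be conducted at two critical junctures: baseline and postintervention". Table 1 schedules the hormone biomarkers at the baseline visit and at the end-of-treatment visit.
- **Analysis.** Section 6.7 offers, for all measurement data, an independent-samples t-test or "the Mann-Whitney U rank sum test, contingent upon the normal distribution and homogeneous variance of the measurement data". Significance is two-sided at 0.05.
- **Check used.** Section 6.2 gives the same pairing of a mean test and a rank test, and names the check: "Continuous variables' normality was assessed using the Shapiro-Wilk test in this study".
- **Sizing.** Section 6.4 works with means: "acupuncture demonstrated a reduction in FSH levels by 20 IU/L", and it assumes that the "control group reduced FSH levels by 14.5 IU/L", with a margin of 3 IU/L.

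No section names a model with baseline FSH as a covariate.

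**The concern.** Two features of the stated analysis are weak for a randomised trial with one baseline and one follow-up measurement.

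First, the test is chosen by looking at the data. A t-test addresses a difference in mean change; a Mann-Whitney test addresses a rank-based quantity. The trial is sized on a difference in means, so a reader cannot tell in advance whether the primary result will be on the scale of the sizing.

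Second, baseline FSH enters only by subtraction. With r below 1 and similar variances at the two visits, women with higher baseline FSH tend to fall more, so a change score still carries part of any baseline difference between the arms. Adjusting for baseline FSH removes that part and usually narrows the confidence interval, using data already collected.

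At stake are the precision of the primary comparison and the clarity of what it estimates.

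**Working it through.** **1. The plan's own figure.** Section 6.4 gives 54 per group with 20 % dropout, α = 0.05 and power 0.90. The formula contains σ, but no value is stated, so the figure cannot be reproduced. Back-solving with a difference net of the margin of 20 − 14.5 − 3 = 2.5 IU/L, equal groups and the one-sided Z as printed:

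N = 2 × (1.645 + 1.282)² × σ² / 2.5² ≈ 2.74 σ²

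σ = 4 gives N = 44, which becomes 44/0.8 = 55 or 44 × 1.2 = 53, both close to 54. So σ near 4 IU/L would fit, but this is inference. The calculation below does not depend on it.

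**2. Inputs for the comparison.** Evaluable women per arm: 54 × 0.8 = 43.2, taken as 43. This is an assumption, because section 6.6 says dropouts will be imputed and kept in the analysis. The correlation r between baseline and follow-up FSH is not in the documents; the range 0.3 to 0.9 is assumed. The variance of FSH is assumed equal at the two visits.

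**3. Variance ratio.** With common variance s²:

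- change score: variance per woman = 2s²(1 − r)
- ANCOVA: residual variance per woman = s²(1 − r²)
- ratio = (1 − r²) / (2(1 − r)) = (1 + r)/2

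| r | Ratio | 43 per arm is worth (43/ratio) | Power at the same n if the change-score t-test has 90 % (two-sided 0.05) |
|---|---|---|---|
| 0.3 | 0.65 | 66 | 98 % |
| 0.5 | 0.75 | 57 | 96 % |
| 0.7 | 0.85 | 51 | 94 % |
| 0.9 | 0.95 | 45 | 91 % |

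Power is Φ((1.960 + 1.282)/√ratio − 1.960).

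**4. Chance imbalance.** Under the same assumptions the slope of change on baseline is −(1 − r). For each 1 IU/L by which one arm happens to start higher, its mean change is expected to be 0.7, 0.5, 0.3 or 0.1 IU/L more negative at r = 0.3, 0.5, 0.7 or 0.9, whatever the treatment. Averaged over randomisations this is zero; in the one trial actually run it need not be.

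**5. Simulation of the rule.** The formula covers only the t-test branch, so the whole rule was simulated: 43 per arm, 2,500 runs per setting, test chosen by Shapiro-Wilk and Levene checks, effect 0.6 SD, normal and log-normal data.

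| r | Normal data: rule vs ANCOVA power | Skewed data: rule vs ANCOVA power |
|---|---|---|
| 0.3 | 0.63 vs 0.80 | 0.71 vs 0.81 |
| 0.5 | 0.79 vs 0.89 | 0.86 vs 0.88 |
| 0.7 | 0.94 vs 0.97 | 0.97 vs 0.96 |

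The rule moved to Mann-Whitney in about 13–15 % of trials with normal data and 64–71 % with skewed data. Type I error lay between 0.042 and 0.059 for all methods. The Monte Carlo standard error at 5 % is √(0.05 × 0.95/2,500) = 0.0044, so this is close to nominal.

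**The case against.** The strongest reply is that a two-sample comparison of change is a valid analysis of the stated outcome and matches the two-mean sizing formula. That stands. Several stronger readings are tempting, and the documents do not support them.

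- **That baseline FSH is ignored.** It is not: the outcome is a change, so baseline is used by subtraction. What is missing is adjustment for it as a covariate.
- **That the result will be biased, or the error rate inflated.** Allocation is randomised 1:1, so the change-score difference is unbiased over randomisations. Only the estimate conditional on an observed imbalance is shifted, and the simulation shows no inflation of type I error.
- **That the gain is large and certain.** The ratio (1+r)/2 needs equal variances, falls away as r nears 1 and does not describe the rank branch. With skewed data, the rule nearly matches ANCOVA at r = 0.5 and slightly exceeds it at r = 0.7.
- **That a rank test can say nothing in IU/L.** A Hodges-Lehmann shift could be reported, and section 6.7 gives means and SDs in any case. But no such estimate is planned, and the shift is not in general the difference in means on which the trial is sized.

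It can also be said that section 6.7 is one generic sentence and that covariates may be set out in a fuller document. That has some force for the missing covariate. It has less for the choice of test, because the article itself states that rule.

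**Conclusion.** The point holds as a free improvement, not as an error of validity. The stated rule lets the data settle whether the primary comparison concerns means or ranks, although the sizing is in mean IU/L, and it does not use baseline FSH as fully as it could.

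In the t-test branch with equal variances, the variance saved runs from 35 % at r = 0.3 to 5 % at r = 0.9. If FSH is strongly skewed, little or nothing is gained in power over the rule at r of 0.5 or more, and the case then rests on having one fixed estimand and on protection against chance imbalance. Confidence in the size of the gain is medium, because neither r nor the variances are in the documents.

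**What to change.** Before the data are analysed, name one primary analysis in section 6.7:

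- ANCOVA of end-of-treatment FSH on arm and baseline FSH, reporting the adjusted difference in IU/L with a 95 % confidence interval from robust standard errors.
- The same model on log FSH, and the rank test, as sensitivity analyses only. The log scale also fits the 30 % relative fall used to define response.
- No choice of the primary test from normality or variance checks on the trial data.

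The same adjustment can be used for the secondary continuous outcomes that have a baseline value, such as the other hormones, SAS and SDS. The cost is a sentence or two of text. It needs no extra visits, samples or participants.

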### Patient and public involvement

6.8

Patients were not involved in the design and conduct of the study. Participants will be able to view the study results via social media.

## Discussion

7

Acupuncture, rooted in traditional Chinese medicine and boasting a millennia-long history, has gained global recognition as a therapeutic modality for diverse medical conditions [25]. Integral to Chinese medicine, acupuncture stands out for its non-invasive nature, convenience, and minimal adverse effects, rendering it applicable in the prevention, treatment, and rehabilitation of numerous ailments [26]. Substantial evidence from both clinical and laboratory studies has highlighted acupuncture's efficacy in addressing inflammation, immune responses, and various chronic gynecological and endocrine disorders [[27], [28], [29]]. Recent years have witnessed significant progress in clinical and experimental research, particularly in the context of POI [12,13,28]. Acupuncture demonstrates distinct advantages in mitigating clinical symptoms of POI, regulating sex hormone levels, revitalizing residual follicles, and restoring menstrual cycles [8,[30], [31], [32]]. Despite these advancements, the precise mechanisms underpinning acupuncture's impact on follicular revival and hormone regulation demand further exploration.

Given the escalating incidence of POI, understanding acupuncture's potential to impede its progression assumes paramount importance [33]. While debates persist regarding the scientific substantiation of acupuncture's benefits, it exhibits promise in treating infertility disorders associated with POI and sex hormone imbalances [34,33]. The advent of RNA Seq technology has become instrumental in unraveling the molecular-level mechanisms of acupuncture [35,36]. Nevertheless, scant attention has been devoted to discerning the individualized effects of acupuncture on POI patients, and the potential inter-individual variations in efficacy remain largely unexplored. Furthermore, the transcriptomic landscape of acupuncture treatment for POI remains a largely uncharted territory.

To address these knowledge gaps, we propose a nested case-control study employing transcriptome sequencing technology to analyze peripheral blood samples from POI patients subjected to acupuncture [37,38]. This approach seeks to elucidate the potential mechanisms governing individual differences in acupuncture efficacy for POI. By scrutinizing transcriptomic changes associated with acupuncture treatment, the study endeavors to evaluate the efficacy of acupuncture for POI and contribute valuable evidence-based insights [[39], [40], [41]]. Ultimately, it aspires to furnish a robust clinical and experimental foundation, paving the way for further investigations into acupuncture's therapeutic potential in POI.

However, it is crucial to acknowledge several limitations accompanying this study. The utilization of serum samples may introduce confounding factors, as local tissue samples might offer greater sensitivity to interference. Despite stringent inclusion and exclusion criteria, the study's results may not comprehensively capture the nuanced mechanisms underlying individual differences in acupuncture efficacy. Additionally, the absence of a sham acupuncture group as a control limits our ability to rule out potential placebo effects influencing observed outcomes. Lastly, the relatively modest sample size employed for transcriptome analysis, although justified considering cost constraints and typical sample sizes in such studies, underscores the challenges inherent in determining optimal sample sizes for transcriptomic investigations.

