**Methods/design:**

Constituting an open-label, nested case-control study, this research endeavors to enroll 108 women diagnosed with POI. Participants will be randomly assigned in a 1:1 ratio to either the study group or the control group, each comprising 54 subjects. Ten patients from each group meeting specific criteria will partake in transcriptome analysis. An additional 10 subjects meeting the study criteria will form a healthy control group. The study group will exclusively undergo acupuncture treatment, while the control group will solely receive Fenmutong. Acupuncture sessions, administered thrice weekly across three menstrual cycles from the fifth day of menstruation, constitute the intervention. Primary outcome measurement rests on Follicle-Stimulating Hormone (FSH) levels, supplemented by secondary assessments encompassing biometric features, hormone biomarkers, anxiety and depression scores, and transcriptome analysis. Baseline measurements precede intervention, with post-intervention evaluations following. The study endeavors to discern specific genes linked to individualized responses to acupuncture. Data analysis, employing SPSS 25.0 software, incorporates a meticulous examination of peripheral blood samples for transcriptome analysis. The investigation aspires to shed light on genetic determinants influencing the effects of acupuncture on women with POI, thereby fostering elevated standards in patient care and management.

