Recent years have witnessed a rise in POI incidence, necessitating an in-depth investigation into its pathogenesis and treatment mechanisms. The advent of transcriptome sequencing technology in 1997 has revolutionized the study of POI's underlying mechanisms. Transcriptome sequencing not only serves as the foundation for identifying new POI-related genes but also facilitates the analysis of immune-related gene regulation, establishing correlations between different genes involved in POI pathogenesis. With approximately 90 genes currently linked to POI, its genetic heterogeneity becomes evident. For instance, studies exposing rats to environmental toxicants and utilizing transcriptome sequencing technology have identified DNA damage repair defects as pivotal in the pathogenesis of POI [[16], [17], [18]].

In this study, our primary objective is to gain a comprehensive understanding of the physiological significance of ovarian dysfunction in POI patients through peripheral blood transcriptome sequencing technology. The interactions between genes and ovarian function play a crucial role in elucidating the association between acupuncture action genes and individual differences observed in ovarian function recovery. To achieve these goals, we have designed a nested case-control study to evaluate the additional benefits of acupuncture treatment for women with POI. Additionally, we aim to investigate the mechanism underlying individual variations in response to acupuncture treatment, utilizing transcriptome gene sequencing analysis on peripheral blood samples. By employing this approach, we aim to systematically explore the potential mechanisms behind the observed individual curative effect differences with acupuncture in women with POI.

Through this research endeavor, we aspire to contribute valuable insights into the therapeutic effects of acupuncture for POI and shed light on the intricate interactions between genes and ovarian function. By understanding the underlying mechanisms, we hope to identify factors influencing the efficacy of acupuncture treatment in women with POI, paving the way for more personalized and effective treatment strategies for this condition. Ultimately, our study aims to contribute to the advancement of knowledge in the field of POI research, potentially improving the quality of life and outcomes for affected individuals.

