### Study design

4.1

The proposed investigation adopts an open-label, nested case-control study design to be conducted at Shenzhen Maternity and Child Healthcare Hospital. A total of 108 participants diagnosed with POI will be recruited for the study, and subsequent random assignment will be executed to allocate these patients into either the study group or the control group. The allocation ratio is set at 1:1, ensuring an equal distribution of 54 subjects in each group. Prior to the commencement of any intervention, explicit informed consent will be procured from all participating patients through the endorsement of a consent form administered by the researchers.

Patients comprising the study group will exclusively undergo acupuncture treatment, while those in the control group will exclusively receive Fenmutong. To gain deeper insights into the mechanisms contributing to individual variations in the therapeutic outcomes of acupuncture, a subset of 10 patients from each group will undergo transcriptome analysis. This subset will encompass patients experiencing a serum FSH level decrease of ≥30 % post-acupuncture intervention, alongside those displaying a decrease of <30 % in serum FSH levels following the intervention. The trial's procedural flow is visually represented in Fig. 1, offering a comprehensive overview of the various stages and interventions integral to the study. Additionally, Table 1 provides meticulous details on the data collection process, delineating specific data points and measurements crucial for the comprehensive execution of the research.

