**Fig. 1 fig1:**
[figure not shown]
Study flow chart. Note: transcriptome analysis included 10 patients in the POI group and 10 patients in the Fenmutong group, with 5 patients with serum FSH levels ≥30 % and 5 patients with serum FSH levels <30 % in both groups.10 healthy women were selected as the control group.

**Table 1 tbl1:** Overview of study visits.

Itern	Screening visit	Baseline visit	Treatment visit		End of treatment visit
			POI group	Control group	
Sign consent	×				
History	×				×
Biometric features	×	×			×
Transvaginal ultrasound	×	×	×	×	×
Routine test	×				×
hormone biomarkers		×			×
transcriptome analysis		×			×
Questionnaires		×			×
Acupuncture treatment			×		
Adverse events			×		

Note: Participants from the POI group will be selected for transcriptome analysis and will only be assessed at the initial screening visit. History, biometric features, routine test results, and transcriptome analysis will be assessed. Biometric features include body mass index (BMI); transvaginal ultrasound includes endometrial thickness, ovarian volume, antral follicle count, and size of ovarian cysts or developing follicles; Routine tests include blood routine examination, liver function, kidney function, routine stool, and urine tests; Hormone biomarkers include luteinizing hormone (FSH), follicle stimulating hormone (LH), total testosterone, progesterone, estradiol, and leptin; questionnaires include Self-Rating Anxiety Scale (SAS) and Self-Rating Depression Scale (SDS).

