### Secondary outcomes

5.2

The principal outcome measure in this study revolves around the alteration observed in FSH levels. This metric serves as a pivotal gauge to evaluate the effectiveness of acupuncture treatment when employed as an adjunctive therapy for POI. The data collection process is bifurcated into two distinct time points: the baseline assessment conducted prior to the study's initiation and a subsequent assessment following the culmination of three menstrual cycles of acupuncture treatments. This meticulous approach aims to provide comprehensive insights into the impact of acupuncture on FSH levels over the specified duration, thereby contributing to the overall assessment of its therapeutic efficacy for POI. In conjunction with the primary focus on FSH levels, this study encompasses an exploration of secondary outcomes to foster a holistic comprehension of acupuncture's impact on POI. Secondary outcome measures encompass biometric features, hormone biomarkers, Self-Rating Anxiety Scale, Self-Rating Depression Scale, and transcriptome analysis. The data acquisition for these secondary outcomes is structured around two pivotal time points: the baseline assessment before study commencement and the post-intervention assessment after the conclusion of acupuncture sessions.

Comparative analysis of these datasets enables researchers to discern alterations in various parameters resultant from acupuncture treatment. Specifically, to scrutinize the distinct genes associated with individual variations in acupuncture's therapeutic effects, gene abundance profiling will be conducted within the study group and juxtaposed with the control group. Transcriptome analysis, performed on peripheral blood samples from 5 participants in each group exhibiting a ≥30 % reduction or <30 % reduction in serum FSH levels post-intervention, aims to unravel the molecular intricacies underlying acupuncture's differential efficacy. An additional 10 subjects, meeting the study criteria, will be enlisted for the healthy control group. The ensuing data analysis will be executed utilizing SPSS 25.0 for comprehensive evaluation.

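### The aim is determinants of response to acupuncture, but the responder contrast and ROC curves are not tied to the baseline sample, and the article contradicts itself on when transcriptome samples are taken

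*Protocol article*

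**What the plan says.** **Aim.** The Abstract (Methods/design) hopes to "shed light on genetic determinants influencing the effects of acupuncture on women with POI". Section 3 (Background) says "we hope to identify factors influencing the efficacy of acupuncture treatment in women with POI", and links this to more personalised treatment.

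**Framing of the analysis.** Section 7 (Discussion): "By scrutinizing transcriptomic changes associated with acupuncture treatment, the study endeavors to evaluate the efficacy of acupuncture for POI". Section 5.2 (Secondary outcomes) first describes comparing the two time points to detect alterations that result from treatment. It then introduces the genes linked to individual variation as a specific case of that comparison.

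**Responder groups.** Section 4.1 (Study design): "This subset will encompass patients experiencing a serum FSH level decrease of" at least 30 %, together with women whose FSH falls by less. Section 6.4 gives five of each per arm.

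**Sample used for the contrast.** Section 5.2 says the transcriptome analysis is "performed on peripheral blood samples from 5 participants in each group exhibiting a" fall on one side or the other of 30 %. It does not date the blood sample. Section 6.2 names DESeq2 without a contrast or time point. It adds that, for genes that differ, "receiver operating characteristic (ROC) curves were constructed to assess their diagnostic performance", again without a contrast or time point.

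**Sampling times.** Section 5.2 places the secondary outcomes, transcriptome included, at "the baseline assessment before study commencement and the post-intervention assessment after the conclusion of acupuncture sessions". The transcriptome row of Table 1 agrees: baseline visit and end-of-treatment visit. The note under Table 1 says otherwise: "Participants from the POI group will be selected for transcriptome analysis and will only be assessed at the initial screening visit".

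**The concern.** A determinant or predictor of response must be in place before the response. The responder label here is the FSH fall over three cycles, known only at the end. An end-of-treatment sample is taken when that fall has already happened, and a change score covers the same window. A blood transcript that simply follows hormone status will then differ between responders and non-responders although it had no part in producing the response.

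An analyst following sections 5.2 and 7 as written could report such transcripts as reasons why acupuncture works in some women. An ROC curve built on them could not guide the choice of patients, because by then FSH itself is known. The conflict over sampling time makes this worse: one reading of Table 1 gives paired samples, the other a single pre-treatment sample.

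**Working it through.** There is no planned figure to reproduce, because the point concerns the time of measurement. The first part compares the text; the second is an illustration on assumed inputs.

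**1. Text side by side**

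| Element | What the article fixes |
|---|---|
| Question | Factors influencing response, so information that precedes it (Abstract, section 3) |
| Outcome label | FSH fall of at least 30 % or less than 30 %, known after treatment (4.1, 5.2, 6.4) |
| Samples | Baseline and end of treatment (5.2, Table 1 row), or initial screening only (Table 1 note) |
| Sample in the responder contrast | Not stated (5.2, 6.2) |
| Contrast and sample for the ROC | Not stated (6.2) |
| Narrative | Change from baseline to post-intervention (5.2, 7) |

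Of the possible inputs, only the baseline sample answers the question in the first row. The text leans towards change.

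**2. Illustration (all inputs assumed, none from the article)**

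Log-FSH has SD 0.35 at baseline, the change in log-FSH has SD 0.35, and the median fall is 30 %. Responder means change ≤ ln 0.7. The gene equals r × standardised current log-FSH + noise, with a within-woman noise correlation of 0.5. It has no influence on response. AUCs for responder status come from 400,000 simulated women and ignore direction.

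*Case A: FSH change independent of baseline FSH.* The post-treatment SD becomes √(0.35² + 0.35²) = 0.495.

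| r | Baseline | Post, scaled per visit | Post, baseline scale | Change, scaled per visit | Change, baseline scale |
|---|---|---|---|---|---|
| 0.3 | 0.50 | 0.60 | 0.63 | 0.60 | 0.64 |
| 0.5 | 0.50 | 0.66 | 0.71 | 0.67 | 0.73 |
| 0.7 | 0.50 | 0.73 | 0.77 | 0.76 | 0.83 |

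*Case B: stable SD of 0.35 at both visits, correlation 0.5.* The change SD is 0.35 × √(2 × (1 − 0.5)) = 0.35, as in case A. Now baseline FSH and change correlate at −0.5, which is regression to the mean.

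| r | Baseline | Post | Change | Baseline, adjusted for baseline FSH |
|---|---|---|---|---|
| 0.3 | 0.57 | 0.57 | 0.64 | 0.50 |
| 0.5 | 0.61 | 0.61 | 0.73 | 0.50 |
| 0.7 | 0.66 | 0.66 | 0.83 | 0.50 |

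**3. A second model at the planned 5 versus 5**

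Post-treatment expression = baseline + b × FSH fall in SD units + noise of SD 0.5, with baseline unrelated to response; 20,000 runs. Mean AUCs for b = 0, 0.5, 1, 1.5, 2:

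- baseline: 0.50 throughout
- end of treatment: 0.50, 0.69, 0.81, 0.88, 0.92
- change: 0.50, 0.83, 0.94, 0.97, 0.98

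In the same runs, a null gene at baseline reached an AUC of 0.8 or more about 7 % of the time. Baseline sampling makes the contrast interpretable; it does not make ten women precise.

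**The case against.** The strongest objection is that the article never chooses the wrong sample. In section 5.2 the word post-intervention can attach to the FSH reduction and need not date the blood. Section 6.2 names no time point. Read literally, the Table 1 note puts sampling before treatment. A reader might infer that the plan takes expression during or after treatment as its measure of determinants. The article does not support that: no transcriptome sample is marked at the treatment visit, and the sample for the contrast is left open. This part of the objection stands.

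Second, section 6.2 calls the ROC diagnostic, and ten healthy women are included, so the curves may separate POI from healthy women. They cannot be called circular as they stand. This also stands, and is a reason to name the contrast.

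Third, paired samples are a proper way to study mechanism, which sections 3 and 7 also give as an aim. Agreed; the fix keeps them.

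Fourth, case B shows that baseline sampling alone does not remove genes that follow hormone status. This stands too, and is why baseline FSH enters the fix.

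Fifth, the choice of sample might be left to the full protocol or analysis plan. This holds only in part. The article itself states the inference, describes the analysis as change, and contradicts itself on sampling time.

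**Conclusion.** The point holds as a mismatch between aim and described analysis, together with a contradiction over sampling times. The article seeks determinants, frames the work as change over treatment, and does not tie the responder contrast or the ROC to the baseline sample. Expression after treatment, or its change over the same window as the FSH fall, can be a consequence of that fall. It supports a statement about correlates, not about determinants or predictors, and it is not evidence of efficacy.

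The logic rests on timing alone. The size rests on assumptions: for a gene with no influence on response, the change-score AUC was 0.60 to 0.83 for r = 0.3 to 0.7, depending on scaling. A reader might infer that baseline expression is automatically free of the problem. It is not: the baseline AUC was 0.50 only when FSH change was independent of baseline FSH, and 0.57 to 0.66 otherwise. These values are not estimates for this trial. The matter touches a secondary outcome and leaves the primary FSH comparison unaffected, but the Abstract features it, so it should be corrected.

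**What to change.** Amend sections 5.2 and 6.2 and Table 1:

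- Use baseline samples for the contrast of women with an FSH fall of at least 30 % versus less, and for any ROC meant to predict response. Adjust for baseline FSH or report it alongside, because percentage fall can depend on it through regression to the mean.
- Report end-of-treatment and change contrasts separately, as mechanistic correlates of response.
- State which contrast each ROC serves: responder versus non-responder, or POI versus healthy. Use baseline POI samples for the healthy comparison.
- Reconcile the Table 1 note with the table row and section 5.2. Keep baseline RNA from all randomised women, since responders are known only afterwards.
- In section 7, do not present transcriptomic change as evidence of efficacy.

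**Cost.** Mostly wording, with no new visit. Baseline RNA has to be stored for all 108 women although 20 of them are planned for transcriptome analysis, and fewer genes will be reportable.
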